## Abstract

**Background:**

Diabetes during pregnancy has negative effects on both mothers and their fetuses. To improve perinatal outcomes and women’s experience of care, the World Health Organization (WHO) suggests implementing health system interventions to enhance the use and quality of antenatal care. The main goal of this study is to implement and evaluate the outcomes of the Centering Pregnancy group care model for pregnant women with diabetes.

**Methods/design:**

The study will consist of three phases: a quantitative phase, a qualitative phase, and a mixed phase. In the quantitative phase, a randomized controlled trial will be conducted on 100 pregnant women with diabetes receiving prenatal care in Tabriz City, Iran. The Summary of Diabetes Self-Care Activities (SDSCA) questionnaire will also be validated in this phase. The qualitative phase will use qualitative content analysis with in-depth and semi-structured individual interviews to explore pregnant women’s understanding of the impact of the Centering Pregnancy group care model on their care process. The mixed phase will focus on the degree and extent of convergence between quantitative and qualitative data.

**Discussion:**

The implementation of the Centering Pregnancy group care approach is anticipated to empower women in effectively managing their diabetes during pregnancy, resulting in improved outcomes for both mothers and newborns. Furthermore, adopting this approach has the potential to alleviate the financial burden of diabetes on healthcare system.

**Trial registration:**

Iranian Registry of Clinical Trials (IRCT): (IRCT20120718010324N80/ Date of registration: 2024-01-03). URL: https://irct.behdasht.gov.ir/trial/74206.

## Background

Pregnancy involves multiple changes in the structure and function of the mother’s body, serving as a biological stress test for her various systems and organs [1]. Diabetes during pregnancy can be categorized into two subgroups: pre-existing diabetes, which includes type 1 or type 2 diabetes, and gestational diabetes mellitus, which is diabetes that develops during pregnancy [2]. Both gestational and pre-existing diabetes result in hyperglycemia, with pre-existing diabetes posing a greater severity and detrimental effects on the health of both mother and fetus [3].

Gestational diabetes is a common complication during pregnancy, typically occurring after the first trimester [4]. It affects around 14% of women globally and has a prevalence of 7.6% in Iran [5, 6]. Gestational diabetes raises the likelihood of negative consequences for both the mother and the baby, including risks of macrosomia, preterm birth, fetal loss, and cesarean delivery. Additionally, it can lead to complications like shoulder dystocia, birth trauma, and neonatal hypoglycemia. Women with gestational diabetes also face a 50% lifetime risk of developing type 2 diabetes [7, 8]. The prevalence of pre-existing diabetes in pregnancy is rising globally, despite being relatively uncommon [9]. While effective blood sugar control during pregnancy can reduce the risk of adverse perinatal outcomes and birth defects, women with pre-existing diabetes remain at a higher risk for unfavorable pregnancy outcomes, including fetal death, maternal preeclampsia, and birth defects [10, 11].

Improving maternal health and reducing child mortality are among the key goals of the United Nations’ Millennium Development Goals [12]. Group-based prenatal care, such as Centering Pregnancy, is a model that leads to a reduction in preterm labor and adverse birth outcomes among women with uncomplicated pregnancies [13]. Moreover, pregnant women with common medical conditions like diabetes who participate in group prenatal care are not at a higher risk of preterm birth, low birth weight, or neonatal intensive care unit (NICU) hospitalization [14].

Centering Pregnancy is an innovative prenatal care model that involves grouping women with similar gestational ages for comprehensive care. This approach fosters behavior modification, social support, and the exchange of knowledge among participants. By creating a positive environment, pregnant women can learn from one another, gain a greater sense of agency over their pregnancies, and benefit from improved education and support. Centering Pregnancy stands out as a distinct and advantageous approach to providing prenatal care [15–17].

Currently, there is a research gap in evaluating the Centering Pregnancy group care model specifically for diabetes due to limited studies conducted in this area [18, 19]. Most of the existing studies have relied on observational designs [20–22], which may be susceptible to confounding factors. Moreover, the majority of studies have been conducted in other countries, particularly in the United States, and findings based on different racial and ethnic groups may not be directly applicable to Iranian women. However, it has been demonstrated that this model can reduce neonatal hospitalization costs by decreasing NICU admissions [23].

Therefore, given the adverse consequences of diabetes in pregnancy, implementing the Centering Pregnancy group care model has the potential to be beneficial in improving the healthcare system’s burden. To enhance self-care practices for pregnant women with diabetes and improve their pregnancy experience, as well as maternal and neonatal outcomes, it is essential to assess the current state of care and gather insights from these individuals using a comprehensive approach. This study will serve as the first investigation in Iran to implement and evaluate the Centering Pregnancy group care model in pregnant women with diabetes, employing a combined methodology to gather comprehensive data.

## Objectives

The overall objective of this study is to implement and evaluate the outcomes of the Centering Pregnancy group care model in pregnant women with diabetes.

## Study design

This research is a study of a convergent parallel mixed methods, and its paradigm is pragmatism. The present study will be conducted in three phases: quantitative, qualitative, and the combination of both quantitative and qualitative phases. In this mixed design, qualitative and QUAN quantitative data will be collected and analyzed simultaneously and independently. Both types of data will have equal priority and value (QUAL + QUAN). Data analysis will be performed separately, and the results will be integrated during the data interpretation stage. The discussion will focus on the degree and extent of convergence between quantitative and qualitative data [24, 25] (Fig. 1).

**Fig. 1 Fig1:**
[figure not shown]
The mixed methods convergent parallel design

## Study phases

### Quantitative phase (phase 1)

#### Study design and setting

The quantitative phase of the present study will involve a randomized controlled trial conducted on 100 pregnant women with diabetes who seek prenatal care at educational and therapeutic hospitals such as Taleghani, Al-Zahra, 29 Bahman, Al-Ghadir (governmental hospitals), as well as Valiasr and Behbood (private hospitals), and health centers in Tabriz city-Iran. Figure 2 shows the flowchart of this phase.

**Fig. 2 Fig2:**
[figure not shown]
Consort flowchart of the trial process

#### Specific objectives

The specific objectives of the quantitative phase are as follows:

To compare the mean scores of diabetes self-care activities in weeks 36–39 of pregnancy between the intervention and control groups (receiving Centering Pregnancy group care model and receiving routine care, respectively), while controlling for baseline scores.To compare the mean scores of self-efficacy in weeks 36–39 of pregnancy between the intervention and control groups (receiving Centering Pregnancy group care model and receiving routine care, respectively), while controlling for baseline scores.To compare the mean scores of pregnancy experience in weeks 36–39 of pregnancy between the intervention and control groups (receiving Centering Pregnancy group care model and receiving routine care, respectively), while controlling for baseline scores.

#### Secondary objectives

The secondary objectives of the quantitative phase are as follows:

To compare the frequency of preterm deliveries between the intervention and control groups.To compare the frequency of cesarean deliveries between the intervention and control groups.To compare the frequency of admission in the NICU between the intervention and control groups.To compare the mean satisfaction scores regarding perinatal care between the intervention and control groups.To compare the mean scores of breastfeeding performance at 6 weeks postpartum between the intervention and control groups.To determine the face validity, content validity, construct validity, and reliability of the Summary of the Diabetes Self-Care Activities (SDSCA) questionnaire in women with gestational diabetes.

#### Eligibility criteria

The study includes pregnant women who have gestational diabetes mellitus (GDM) or type 2 diabetes and are at least 24 weeks pregnant. They must be able to attend group sessions in Tabriz city for a duration of 8 weeks before childbirth. However, the study excludes women with multiple pregnancies, major fetal anomalies, concurrent medical conditions, psychiatric disorders, and advanced or complicated diabetes. These criteria are important for ensuring the study focuses on a specific group of participants who meet the requirements and can provide valuable insights into the research objectives.

#### Sample size

The sample size in this study was calculated based on the variable of diabetes self-care activities using the G-Power software. According to the results of the study by Al-Hashmi et al. [26] regarding the variable of diabetes self-care activities, and considering M_1_ = 3.1 and M_2_ = 3.7 (assuming a 25% increase due to intervention), SD_1_ = 1.2 and SD_2_ = 1.2, two-sided α = 0.05, and Power = 90%, the sample size was calculated to be 45 participants. Taking into account a 10% dropout rate, a final sample size of 50 participants in each group was considered.

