##### Summary of the diabetes self-care activities questionnaire

The SDSCA is an assessment tool used to measure various aspects of diabetes management. It consists of 11 items that cover areas such as diet, exercise, glucose monitoring, foot care, and smoking. Responses are rated on a scale from 0 to 7 days per week [34]. The tool has shown good internal consistency with high inter-item correlations (0.47) and moderate test-retest reliability (0.40). However, for pregnant women with diabetes, only three areas (diet, exercise, and glucose monitoring) are evaluated because foot care and smoking are not relevant in this context [35].

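### The printed inputs need 86 women per group for 90% power, not 45; at 45 per group the power for 3.1 versus 3.7 is about 65%

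*Protocol article*

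**What the plan says.** All of the sizing is in the Sample size section of the protocol article. The calculation was "calculated based on the variable of diabetes self-care activities using the G-Power software". The means are given as "M_1_ = 3.1 and M_2_ = 3.7 (assuming a 25% increase due to intervention" and the spread as "SD_1_ = 1.2 and SD_2_ = 1.2". The error rates and the result follow: "two-sided α = 0.05, and Power = 90%, the sample size was calculated to be 45 participants". The next sentence allows for 10% dropout and arrives at 50 in each group, so 45 is a per-group figure. This agrees with the total of 100 women (Study design and setting) and the 1:1 allocation (Randomization and blinding).

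The Specific objectives and Data analysis sections plan to compare the groups by ANCOVA, controlling for baseline. The Sample size section states no correlation between baseline and follow-up. The only stability figure given for the instrument, in the section describing the questionnaire, is "moderate test-retest reliability (0.40".

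**The concern.** A standardised difference of 0.5 at 90% power with a two-sided 5% test is a familiar case that needs about 85 per group. A figure of 45 is about half of that. In the same sentence, the percentage increase does not match the two means.

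Self-care activities is one of the three primary outcomes and the only one used for sizing. If 90% is wrong, a non-significant result will be read as good evidence that group care does not improve self-care by the stated amount. The section accepts a one-in-ten chance of missing that effect. On the comparison its inputs describe, the chance is about one in three.

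**Working it through.** **Inputs (Sample size section):** means 3.1 and 3.7; SD 1.2 in each group; two-sided α = 0.05; power 90%; stated n = 45 per group, 50 after dropout.

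**1. The plan's own figures.** The dropout step reproduces: 45/(1 − 0.10) = 50. The 45 does not.

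- Difference = 3.7 − 3.1 = 0.6, so d = 0.6/1.2 = 0.50.
- Normal approximation: n = 2(1.960 + 1.282)²/0.50² = 2 × 10.51/0.25 = 84.1, so 85 per group.
- Noncentral t (the independent-means t test): n = 85.03, so 86 per group. With 10% dropout, 86/0.9 = 95.6, so 96 per group or 192 in total.

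**2. Power at the planned size.** The noncentrality is d√(n/2) = 0.50 × √22.5 = 2.37 at 45 per group.

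- 45 per group: 65.0% (normal approximation 66.0%).
- 50 per group, no dropout: 69.7% (normal approximation 70.5%).
- Difference detectable at 45 per group: 0.83 with 90% power, 0.72 with 80% power.

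**3. The percentage.** 0.6/3.1 = 19.4%. A 25% increase is 3.1 × 1.25 = 3.875, a difference of 0.775 and d = 0.646. That needs 51.4, so 52 per group; power at 45 is 85.8%.

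**4. Other readings of the printed inputs.**

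| Reading | n per group |
|---|---|
| d = 0.50, one-sided, 90% | 70 |
| d = 0.50, two-sided, 80% | 64 |
| Difference 0.55 to 0.65, SD 1.15 to 1.25, two-sided, 90% (normal approximation) | 66 to 109 |
| d = 0.646, two-sided, 90% | 52 |
| d = 0.646, one-sided, 90% | 42 |

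None gives 45. A paired or one-sample t test with d = 0.5 gives 44 in total. That may be where the figure came from, but the document does not show it, and that test does not fit two independent randomised groups.

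**5. Baseline adjustment.** ANCOVA multiplies the SD by √(1 − r²), where r is the baseline-to-follow-up correlation. The document gives no r, so the values below are assumed. At difference 0.6 and 45 per group:

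| r | Power |
|---|---|
| 0.3 | 69.1% |
| 0.4 | 72.6% |
| 0.5 | 77.3% |
| 0.6 | 83.5% |

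At r = 0.4, 90% power needs 71.6, so 72 per group. For 45 per group to give 90%, 85.03(1 − r²) = 45, so r = √(1 − 45/85.03) = 0.686. Solving the power function directly gives 0.690.

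**The case against.** The strongest reply is that 65% is not the only defensible figure. The section names two incompatible effects and does not show which is the slip. If 25% was intended and 3.7 is a misprint, power at 45 per group is 85.8%; with M2 rounded to 3.9 it is 87.9%. If the SD were also 1.15 rather than 1.2, a difference of 0.8 would need exactly 45. The planned analysis is ANCOVA, so an unadjusted power figure understates what the trial will have. The two points also combine: at a difference of 0.775 and an assumed r = 0.4, power at 45 is 91%. Finally, the 0.40 is a test-retest figure for the general questionnaire. It is not the correlation between baseline and weeks 36–39 for the three-domain score used here.

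Much of this stands as caveat. The intended effect is unsettled, 0.40 is only a rough guide to r, and one in three applies to the unadjusted comparison; at r = 0.4 and difference 0.6 about 27% of trials would miss.

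It does not rescue the statement as printed. Every route to 45 replaces a printed value (M2, or M2 and the SD) or brings in a correlation that the section never mentions. With the printed means and SD, that correlation would have to be about 0.69, and nothing in the document supports it. Nor is this a matter of condensation: the article prints a complete set of inputs and a result that does not follow from them.

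**Conclusion.** The concern holds. For 3.1 versus 3.7, SD 1.2 and a two-sided 5% test, 90% power needs 86 evaluable women per group. The planned 45 give 65.0%, assuming two independent groups and no baseline adjustment, which is all that the stated inputs describe. Adjustment at assumed correlations of 0.3 to 0.6 raises this to between 69% and 83%, still short of 90%. The 25% label is a separate error: it does not match 3.7, and with SD 1.2 and no adjustment it does not produce 45 either. The 90% claim for a primary outcome is therefore wrong as written and must be corrected.

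**What to change.** First settle which effect was intended (3.7, or a 25% increase) and which G-Power test was run. Then rewrite the sample size statement, keeping 50 per group. If 3.7 stands:

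*With 45 evaluable women per group, a two-sided 5% test has 65% power for means of 3.1 and 3.7 (a 19% increase, SD 1.2), and 90% power for a difference of 0.83.*

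If 25% was meant, change M2 to 3.875 and state 86% power at 45 per group, or 52 evaluable per group for 90%. If a gain from ANCOVA is claimed, state the assumed baseline correlation, the basis for it and the resulting power (about 73% at r = 0.40 with M2 = 3.7).

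This costs wording only. No extra women are needed, but the stated power becomes less favourable. Keeping 90% power for 3.1 versus 3.7 without relying on adjustment would take 96 women per group after 10% dropout, or 192 in total, instead of 100.

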#### Procedure

A comprehensive description of the research, including its objectives and the methods of implementation, will be provided to the participants. Detailed explanations regarding the benefits of implementing this model in improving lifestyle and mitigating the consequences of diabetes on both the mother and the fetus will be emphasized. Moreover, it will be emphasized that no adverse effects have been observed on women and their fetuses as a result of this study. Additionally, the costs associated with transportation for attending sessions will be covered to encourage active participation. Those interested in participating will be asked to provide informed written consent through a consent form. Strict confidentiality and anonymity will be maintained in reporting the results, ensuring the privacy of participants. Participants will also be informed of their right to withdraw from the study at any time without facing any penalties or obligations. Subsequently, for those willing to participate, they will be assigned to the study groups accordingly.

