### Management of missing data

To minimize missing data, interviews will be conducted by the research team to complete questionnaires and checklists. Strategies including informed consent, comprehensive follow-up data collection, standardized checklists, and frequent follow-ups will reduce loss to follow-up. In cases of non-adherence or withdrawal, participant outcomes will still be investigated and reported. Missing data will be addressed using multiple imputation, and sensitivity analysis will compare results of modified intention-to-treat analysis with imputed data analysis.

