#### Sample size and sampling

The selection of participants will be based on the objective of the study, which takes place after the completion of training sessions. Maximum diversity will be taken into consideration regarding individual, social, and maternal characteristics. The sampling process will continue until information saturation is achieved, which means that no new information or codes will be obtained.

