## Discussion

The WHO recommends the provision of health system interventions to improve the use and quality of antenatal care in order to enhance perinatal outcomes and women’s experience of care [46].

Antenatal care can be delivered through individual or group-based approaches [47]. In low-risk pregnant women, group antenatal care has been shown to yield improvements in stress levels, self-confidence, knowledge, motivation for healthy behaviors during pregnancy, and active engagement in healthcare practices [48].

Women diagnosed with diabetes during pregnancy often experience shock and anxiety. They may also feel guilt regarding the potential effects on their unborn child. These feelings of anxiety and remorse can have a negative impact on their overall pregnancy experience [49, 50]. It has been shown that group-based antenatal care has a positive impact on the psychosocial well-being of women with higher levels of stress or lower personal coping resources [51].

Group-based antenatal care, specifically the Centering Pregnancy model, has been associated with higher utilization of long-acting reversible contraception and increased likelihood of postpartum oral glucose tolerance testing in women with diabetes. However, no significant differences in adverse outcomes were found between group-based and individual care, warranting further research [19].

Lifestyle interventions can enhance women’s self-management of diabetes and reduce stress and anxiety during pregnancy [52, 53]. Education regarding GDM control, healthy eating, and physical activity are practical interventions that improve self-care and empower women with diabetes [54, 55]. Centering Pregnancy group prenatal care model, has demonstrated encouraging outcomes in improving nutrition and lifestyle among women with diabetes [32]. However, existing studies on the Centering Pregnancy model have predominantly focused on healthy pregnant women, and there is a lack of qualitative or mixed-methods research specifically investigating its effectiveness in pregnant women with diabetes [48, 56–58]. Nevertheless, it is recommended to consider implementing this care model for high-risk women to enhance a comprehensive understanding and achieve better outcomes [14, 59].

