### Strengths and limitations

The present study will be the first of its kind in Iran to implement and evaluate the Centering Pregnancy group care model in pregnant women with diabetes using a mixed methods approach. Other strengths include the use of randomization methods to prevent selection bias in the quantitative phase and the validation of the SDSCA questionnaire, which measures self-care activities, in Iranian women with GDM and pregnant women with type 2 diabetes for the first time. This questionnaire can serve as a standardized and widely used tool for assessing self-care activities in these women in future studies. Furthermore, exploring the experiential understanding of women with diabetes in pregnancy regarding this group care model can provide healthcare professionals with greater knowledge about women’s experiences with diabetes and inform practical interventions for reducing the risk of diabetes in women.

The study has several limitations. Firstly, the reliance on self-report measures, such as the SDSCA questionnaire, may introduce recall bias or social desirability bias. Additionally, there are constraints associated with financial limitations the ability to assess long-term outcomes. Another limitation is the lack of blinding among the providers and participants, which is inherent to the nature of the intervention and could potentially bias the results. However, the statistical analyst will be unaware of the group assignments during the analysis, minimizing this bias. Furthermore, since this type of care is being implemented for the first time in Iran, it relies on the cooperation and acceptance of women, which could lead to attrition bias in the 8-week intervention. Lastly, the generalizability of the study’s findings is limited to women with gestational diabetes and low-risk overt diabetes.

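### Before randomisation recruiters stress the model's benefits and claim no harm from a study not yet run; this can add expectation bias to unblinded self-reported outcomes, and analyst blinding cannot remove it

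*Protocol article*

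**What the plan says.** All references are to the protocol article.

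- **Recruitment message.** Under Procedure, the points to be emphasised to candidates include "Detailed explanations regarding the benefits of implementing this model in improving lifestyle and mitigating the consequences of diabetes on both the mother" and the fetus. They are also to be told that "no adverse effects have been observed on women and their fetuses as a result of this study".
- **Order.** Consent follows, and then: "Subsequently, for those willing to participate, they will be assigned to the study groups accordingly". Both future arms therefore hear the same message.
- **Evidence.** Background describes a research gap for this model in diabetes, with few studies and most of them observational. Discussion says of women with diabetes that "no significant differences in adverse outcomes were found between group-based and individual care, warranting further research". It also reports encouraging results for nutrition and lifestyle.
- **Blinding.** Randomization and blinding leaves participants, caregivers, outcome assessors and providers unblinded. Only the analyst is blinded, and the section ends by saying that analysis and interpretation stay free of bias as a result.
- **Outcomes and collection.** Outcomes names three primary questionnaire scores: self-care activities, self-efficacy and pregnancy experience. Management of missing data says that "interviews will be conducted by the research team to complete questionnaires and checklists".
- **Qualitative interviews.** Only women in the group care arm are eligible. Selection is by study objective, "which takes place after the completion of training sessions".
- **Limitations.** Strengths and limitations admits recall and social desirability bias, and the lack of blinding of providers and participants. It then says that "the statistical analyst will be unaware of the group assignments during the analysis, minimizing this bias".

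**The concern.** A study described throughout in the future tense cannot have observed anything, so the no-harm sentence is wrong whatever the trial later shows. The benefit message presents as settled, for clinical consequences, what the trial is meant to find out.

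The statistical issue is what follows. Once allocated, a control woman knows that she is not receiving the care she was told is beneficial, and an intervention woman knows that she is. Each then answers questions on self-care, self-efficacy and pregnancy experience, put to her by someone who may know her arm. A difference in how the arms answer would look the same as a treatment effect on these scores. A reader of the limitations would be told that this has been dealt with when it has not.

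**Working it through.** **1. Can the no-harm statement be true?** The trial is prospective, and the Data Availability statement says that no datasets have been generated. No observation from this study exists to be reported to candidates.

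**2. Does the benefit message match the article's own evidence?** Only in part. On lifestyle, Discussion reports encouraging results, so that half has some support. On the consequences of diabetes for mother and fetus, Discussion reports no significant difference in adverse outcomes and calls for more research. That half goes beyond the evidence cited.

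**3. Where does the bias enter, and can analyst blinding reach it?** The sequence is: message, allocation, knowledge of arm, questionnaire answered in an interview, score recorded, arms coded, analysis. Expectation acts before the score is recorded. Coding the arms afterwards changes no recorded value, so the between-arm difference is the same whether or not the analyst knows the arms. Analyst blinding guards against choices made during analysis and nothing earlier.

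**4. Can the qualitative interview come before the primary assessment?** Eligibility starts at 24 weeks and the programme lasts 8 weeks, so a woman who starts at once finishes at about 24 + 8 = 32 weeks. The primary questionnaires are due in weeks 36–39. The qualitative interviews follow the sessions, and no order relative to those questionnaires is given. They may therefore come first, in the intervention arm only.

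**5. How much could a reporting shift matter?** The article gives no size for the bias, so this is an assumption shown over a range.

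Inputs from Sample size: SD 1.2 in each arm, two-sided α 0.05, planning difference 3.7 − 3.1 = 0.6, 45 per group before dropout, and 45/(1 − 0.10) = 50 per group after it. The 45 is used here only as the number analysed. It does not follow from the stated inputs: a two-sided two-sample calculation at 90% power gives 85 per group. That is a separate matter, and this point does not rest on it.

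With no true effect and a differential shift *b*, in an unadjusted comparison (normal approximation):

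- SE = 1.2 × √(2/45) = 0.253
- P(significant) = 1 − Φ(1.96 − b/SE) + Φ(−1.96 − b/SE)
- b = 0.2: b/SE = 0.79, so 1 − Φ(1.17) + Φ(−2.75) = 0.121 + 0.003 = 0.124
- b = 0.3: b/SE = 1.19, so 1 − Φ(0.77) + Φ(−3.15) = 0.219 + 0.001 = 0.220

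| Assumed shift (days/week) | Share of 0.6 | 45 per group | 50 per group |
|---|---|---|---|
| 0 | 0 | 5.0% | 5.0% |
| 0.1 | 1/6 | 6.8% | 7.0% |
| 0.2 | 1/3 | 12.4% | 13.3% |
| 0.3 | 1/2 | 22.0% | 24.0% |
| 0.5 | 5/6 | 50.7% | 54.9% |

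The smallest significant difference is 1.96 × 0.253 = 0.50 days/week with 45 per group. A reporting shift of about that size would reach significance by itself roughly half the time.

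**The case against.** Several stronger readings are tempting, and the article does not support them.

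- **That Discussion contradicts the no-harm statement.** It does not. Finding no significant difference in adverse outcomes is compatible with having seen no harm, and Background says that women with conditions such as diabetes are not at higher risk in group care. The fault in the sentence is that it credits the observation to this study. It may be a slip for the model, but it still needs correcting. The consent form is not shown, so its content cannot be judged.
- **That women are interviewed by the staff who treated them.** The article says only the research team, and lists outcome assessors separately from intervention providers. A researcher assists at the sessions, so overlap is possible, but it is not stated.
- **That the qualitative interviews contaminate the primary outcomes.** The order is left open, sampling is purposive so not every intervention woman is interviewed, and the stated aim is neutral.
- **That the bias must favour the intervention.** Both arms hear the message. Controls told of lifestyle benefits might improve or over-report their self-care, and social desirability in interviews can raise scores in both arms. A shift toward the intervention is likely, not certain.
- **That 12–22% estimates this trial's error rate.** It is arithmetic on an assumed shift, which nothing in the article ties to the script or the interviews. The planned analysis is a baseline-adjusted ANCOVA, not the unadjusted comparison used here. Adjustment for baseline would not remove a shift that arises after allocation, though the percentages would differ.

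It is also fair that participant blinding is not feasible here, that the article already discloses self-report bias and part of the blinding problem, and that interviews were chosen to limit missing data. What remains is the recruitment wording, the unordered interviews and the remedy wrongly claimed for the bias.

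**Conclusion.** The point holds at moderate strength. Three things are established from the text: the no-harm sentence cannot be true of a study not yet run; the benefit message on clinical consequences exceeds the article's own evidence; and analyst blinding cannot minimise a bias that arises when outcomes are reported and recorded. The limitations also omit the unblinded outcome assessors.

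That the framing adds differential bias is plausible but not shown, and its size is unknown. The 12–22% range rests on an assumed shift of 0.2 to 0.3 days/week, SD 1.2, 45 per group, no true effect and no baseline adjustment. The concern applies mainly to the questionnaire scores, including satisfaction and breastfeeding performance. It is weaker for preterm birth, cesarean section and NICU admission.

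**What to change.** 1. **Procedure:** replace the emphasis on benefits with a neutral script saying that two forms of care are compared because it is not known which is better. Delete the no-adverse-effect sentence.
2. **Qualitative phase, Sample size and sampling:** state that an intervention woman's interview takes place only after her 36–39 week questionnaires are complete.
3. **Strengths and limitations, and the last sentence of Randomization and blinding:** limit the claim for analyst blinding to bias during data analysis, and list unblinded outcome assessors as a limitation.
4. **Where existing staffing allows:** have the questionnaires collected by team members who neither led nor assisted at the sessions.

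Self-completion of the questionnaires is optional. It would reduce interviewer influence but may leave more blank items, which the interviews were meant to avoid, and participants would still know their arm.

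The cost is wording and procedural changes with an ethics notification, and possibly slightly slower recruitment. No change to the sample size or the care given is needed.
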